**SUMMARY**

Severe anaemia is a frequent cause of admission to hospitals in tropical Africa and about 10% of such children die. In endemic countries, anaemia has multiple causes such as nutritional deficiencies, infections and haemoglobinopathies. However, *Plasmodium falciparum* infection is believed to be the major contributory factor to the aetiology of severe anaemia. Severe anaemia is usually treated by blood transfusion although transfusion carries the attendant risk of transmission of HIV and other blood-borne infections. Thus, there is a need to explore novel strategies to reduce the incidence of severe anaemia in high-risk groups such as children with suboptimal haemoglobin levels because these children are at increased risk of developing severe anaemia if they develop a malaria infection before their haemoglobin level has normalized. Therefore, it is proposed to study whether monthly chemoprevention with sulphadoxine/pyrimethsmine (S/P) given during malaria transmission season can protect Gambian children from developing severe anaemia. After receiving treatment from the hospital, 1200 Gambian children with a haemoglobin concentration of less than 7 g/dL will be randomised to receive either monthly SP or placebo during the rest of the malaria transmission season. Morbidity will be monitored throughout the rainy season. Study subjects will be seen at the end of the dry season to document morbidity and mortality.

The primary endpoint of the trial will be the proportion of children with haemoglobin concentration of less than 7g/dL at the end of the malaria transmission season. An important secondary end-point will be the number of OPD attendances with malaria at the end of the malaria transmission season.

**RESEARCH PROPOSAL**

**1.0 Background to the study**

Anaemia is an important public health problem in sub-Saharan Africa with major social and economic implications. Anaemia causes decreased exercise tolerance and intellectual performance and leads to impairment of normal development. In endemic countries, the prevalence of anaemia in the community is estimated to be 49-89% and that of severe anaemia 1.3-6.4% 1-6. The prevalence of severe anaemia in hospitalised patients is estimated to be in the range of 7-29%7-12. In malaria endemic countries, the incidence of severe anaemia and age specific rates of anaemia correlate strongly with the intensity of *Plasmodium falciparum* malaria transmission, and significant haematological recovery has been seen after malaria control trials13,14. In endemic countries, anaemia has multiple causes such as nutritional deficiencies, infections and haemoglobinopathies. However, *P. falciparum* infection is believed to be a major contributory factor to the aetiology of severe anaemia**.**  Though severe anaemia is an important complication of falciparum malaria, it has not received as much attention from the research community in recent years as cerebral malaria. In areas of seasonaltransmission, cerebral malaria is the dominant form of severe malaria15. In contrast, in areas of high transmission, severe anaemia in young children is the most prevalent form of severe malaria16. Although mortality from severe anaemia, about 10%, is less than that from cerebral malaria (20%-30%), it is likely that several hundred thousand deaths occur from this condition each year.

Prevention of the development of anaemia in children who experience malaria infection depends on both effective parasite clearance and enhancement of the bone marrow response 17-19. Thus, effective antimalarial drugs should reduce parasite persistence and quicken haematological recovery. Despite increasing evidence of widespread resistance and the coincidental increase in prevalence in severe malaria anaemia, chloroquine remains the officially recommended treatment for uncomplicated malaria in The Gambia and many other African countries. Resistance of *P. falciparum* to chloroquine was first detected in The Gambia in 1986, much later than in East Africa, but resistance has subsequently become increasingly prevalent20. A national survey undertaken in 1987 showed an overall prevalence of R1/R2 resistance of 5%: the highest prevalence (16%) was found in the central part of the country, the lowest (<1%) in the Western Region where chloroquine was most widely available21. However, by 1992 the prevalence of R1/R2 resistance among children seen at MRC Fajara had increased to 51%22 and the following year a 65% level of R1/R2 resistance was found among children who presented to the health centre at Farafenni23. In both studies, children treated with chloroquine had lower PCV’s than those treated with S/P one month after presentation. In a more recent study undertaken in 1998, a R1/R11 resistance level of 30% was found in Farafenni24.

Blood transfusion remains the mainstay of treatment for severe anaemia. However, providing a safe and reliable blood transfusion service is a very challenging task in many resource poor health facilities in sub-Saharan Africa and the rapid spread of HIV infection means that the risk of transfusion is substantial25. Severe anaemia is often unrecognised because the signs and symptoms of anaemia are non-specific and it is likely that many such children die in the community before they can receive appropriate treatment. Thus, in the absence of an affordable, safe and effective vaccine, there is an urgent need for new inexpensive strategies that will prevent the development of severe anaemia especially in high-risk groups such as children with suboptimal haemoglobin levels. These children are likely to be at increased risk of developing severe anaemia if they experience malaria infection before their haemoglobin has returned to the normal range. Such strategies include intermittent preventive treatment with an effective antimalarial, insecticide treated bed nets (ITNs) and iron supplementation.

### Chemoprophylaxis and intermittent preventive treatment

Antimalarial chemoprophylaxis in endemic countries has been shown to reduce malarial morbidity, school absenteeism, and all cause mortality but it is no longer advocated because of concerns over its possible effect on the development of resistance, logistics constrains and its potential effect on the development of natural immunity. Chemoprophylaxis can lead to loss of acquired immunity or delay its development and this can potentially cause an increase in episodes of clinical malaria when the intervention is withdrawn. To take advantage of the protective effects of chemoprophylaxis whilst reducing its possible adverse effect on the development of natural immunity to malaria, intermittent preventive treatment (IPT) with an effective an antimalarial has been advocated. IPT involves giving a full treatment dose of an antimalarial drug at specific times, regardless of the presence or absence of malaria parasites. Since treatment is only given on an intermittent basis, this intervention is less likely to interfere with the development of immune responses than sustained chemoprophylaxis. The results of trials conducted using IPT have so far been encouraging.

To determine whether children who had experienced an attack of severe malarial anaemia might benefit from a limited period of chemoprophylaxis, we undertook a pilot trial in 1994 in which MaloprimR (pryrimethamine/dapsone) chemoprophylaxis was given after children had been discharged from hospital. Children who received chemoprophylaxis had fewer episodes of malaria. However, there was no significant difference in the mean haematocrit between those who received chemoprophylaxis and the control group at the end of the follow-up. This was most likely due to the fact that chemoprophylaxis was only started after the end of main malaria transmission season when there was hardly any transmission of malaria taking place26

# Insecticide treated nets

Insecticide treated-mosquito Nets (ITNs) are a key malaria control tool. Several trials have shown ITNs to be a promising approach to malaria control in areas of Africa, Asia and the Pacifics. A recent Cochrane reviewe27 concluded that ITNs reduce overall mortality by about 20% in Africa (range 14%-29%28-30) and clinical attacks of malaria by 50%. Overall, mean haematocrit was 1.4% higher among children sleeping under ITNs compared to those without nets. A study in Tanzania showed that ITNs had a protective efficacy of 62% against anaemia31.

## Iron supplementation for the prevention anaemia

It has been shown that a considerable number of children with severe malaria are iron deficient32. Several studies haveattempted to evaluate the risk benefit of iron supplementationin malaria-endemic areas. Some studies reportedthat iron supplementation increasedthe risk of acquiringor reactivating malaria, whileothers reported no significantadverse effects. Difference in malaria endemicity, trial design, endpoints and dosage regime may have accounted for these contradictory results33-43 . Recently, a trial in an area of intense malaria transmission in Southern Tanzania assessed the impact of iron supplementation (2mg/kg given daily between 2 and 6 months of age), malaria chemoprophylaxis (pyrimethamine /dapsone), both or neither, on the prevention of severe anaemia in infants44. Iron supplementation had a protective efficacy of 28.8% (95% CI 6.3 –45.8%) against the development of anaemia and it did not increase the risk of malaria. In another more recent study in an area of seasonal transmission intermittent treatment with S/P plus iron or S/P alone reduced the incidence of severe malarial anaemia and clinical attacks of malaria48.

**2.0 Objectives**

**2.1 Goal:**

To contribute to the development of evidence based strategies for preventing morbidity / mortality associated with malaria and anaemia.

**Specific objectives:**

1. To assess the effectiveness of monthly with S/P on haematological recovery in children who have been treated for severe anaemia.
2. To measure compliance with the intervention
3. To investigate whether or not infection with chloroquine and S/P resistant strains contributes to the pathogenesis of severe anaemia

3.0 Study design and methods

3.1 Study site:

The study will be based at the 75-bed paediatric unit of The Royal Victoria Hospital (RVH), which is located in the capital, Banjul. This is the main referral hospital for the country. The paediatric unit admits about 7000 children a year, of whom about 800 are anaemic (PCV < 33%). About 250 children with severe anaemia are transfused each year. Children seen at the MRC Hospital will also be eligible for enrolment in the study. Among Gambian children, malaria is the most important cause of anaemia.

### **3.2 Malaria in The Gambia**

Transmission of malaria in The Gambia is seasonal. The climate is typical of sub-Sahelian Africa, with a long dry season which lasts from November-June, followed by a relatively short rainy season from July-October. Rainfall averages about 600 mm per year. Morbidity and mortality from malaria follow this pattern, both occurring more frequently during the rainy season, with a peak in the month of October. *P. falciparum* is the dominant species, being responsible for all severe diseases and for over 95% of clinical attacks. A few cases of clinical malaria are caused by *P. malariae;* *P. ovale* is seen rarely. In rural areas, children experience 0.5-1.0 clinical attacks of malaria a year. Over 90% of clinical attacks occur during the rainy season. Parasite and spleen rates in children aged 1-4 years range from 25% -50%. Acute respiratory infection and malaria are the most common causes of death in children who survive the first month of life. Malaria causes about 4% of deaths in infants and 25% of deaths in children 1- 4 years of age.

Chloroquine is still the officially recommended first line treatment for uncomplicated malaria, but sulphadoxine/pyrimethamine is used widely and quinine is used for the treatment of severe malaria. Anti-malarials can be purchased in several pharmacies in Greater Banjul. Bed nets are used widely in rural areas and The Gambia Government makes permethrin available at a modest cost at the beginning of the malaria transmission season.

**3.4 Enrolment of children**

Children will be enrolled from the paediatric unit of the Royal Victoria Teaching Hospital, Banjul, the MRC Hospital, Fajara, Brikama Health Centre or Essau Health Centre during the first year of the study. The study will be extended to WEC clinic in Sibanor during the second year . Study subjects will be enrolled by non-coercive methods if they met the inclusion criteria and had none of the exclusion criteria.

Inclusion criteria:

1. Age: 3 months to 9 years.
2. Haemoglobin less than 7 g/dL
3. Residence within 30 km of the study centre and availability for the duration of the study period.
4. Informed consent to participate in the study given by the parent or guardian.

## Exclusion criteria:

1. Simultaneous participation in any other trial.
2. Allergy to sulpha drugs.
3. Residence > 30 km from the recruitment site.
4. Lack of consent.

3.5 Screening process and enrolment

All children in the right age group who present to the ward/OPD will have their haemoglobin concentration measured and blood film examined for the presence of malaria parasite. Children with a haemoglobin concentration of less than 7 g/dL will be offered assessment by a project doctor. If assessment is permitted, and the patient fulfils the entry criteria, then written consent will be sought from the parent/guardian. A screening record will be maintained to log all patients who are considered as potential patients but who are excluded. The study will be explained in the parents/ guardians’ preferred language, and written informed consent will be obtained on approved forms.

On entry into the trial a detailed clinical history, drug history, family history and information on bednet usage and impregnation will be obtained. The study physician will examine the child, document nutritional status and record the findings in a case report form. In addition, a detailed address will be obtained. Each study child will be provided with a photo ID card to facilitate identification at each contact.

A5-ml baseline blood sample will be obtained from the first 142 patients seen at the Royal Victoria Teaching Hospital or MRC Clinic for determination of the following:

- Hb, red cell indices, white cell and platelet count (Coulter counter)
- Reticulocyte count
- Markers of iron status (serum iron and ferritin) (first 100 children)
- Sickling test and, if positive, haemoglobin electrophoresis
- Stool examination for hookworm and other parasites (first 100 children)

Other investigations such as chest x-ray and urine examinations will be carried out as clinically indicated. Whenever possible the cause of the anaemia will be determined

3.6 Inpatient management

Children will be treated with parental quinine and given a standard dose of SP on discharge from hospital. In the case of children with impaired consciousness, lumbar puncture will be carried out to exclude concomitant meningitis. Children with a haemoglobin concentration of less than 5 g/dL and/or signs of respiratory distress will be scheduled for immediate transfusion with whole blood in accordance with national guidelines. All patients will received iron for 28 days , treatment starting at the time of their discharge from hospital when their malaria had been treated. Patients will be treated for other conditions as clinically indicated. Children will be kept in hospital until all signs of respiratory distress has subsided and until Hb measurements show an increase in Hb compared to the admission Hb. Patients will be asked to return for follow-up 7 days after admission. Before discharge from hospital, each patient will be provided with a photo ID card and the address of the patient obtained.

3.7 Treatment regimens

Treatment will be given as follows:

S/P (tablets containing 500 mg sulfadoxine/ 25 mg pyrimethamine) at an approximate dose of 1.25 mg pyrimethamine/25 mg sulphadoxine per kg stat dose.

IM Quinine: 20 mg/kg loading dose, then 10 mg/kg 12 hourly for 5 days.

Iron will be given as syrup at a target dose of 2 mg/kg elemental iron.

3.8 Assessment of resistance to chloroquine and antifolates

To investigate whether or not infection with chloroquine or S/P resistant parasites contributes to the pathogenesis of severe anaemia in Gambian children, filter paper blood samples will be collected from the first 100 children entered into the study who have *P.falciparum* parasitaemia and an equal number of aged matched children who attend the OPD clinic with uncomplicated symptomatic malaria. Nested PCR on extracted DNA will be used to tested for mutation in genes associated with resistance; *Pfcrt* and *Pfmdr* for chloroquine and DHRF / DHPS genes for S/P using standard techniques45,46

.

3.9 Discharge from hospital

Study subjects will be individually randomised into either the S/P or the placebo group in a 1:1 fashion at the time of discharge from hospital, although chemoprophylaxis will not be started for another week as the children are likely to have received antimalarials whilst in hospital. Randomisation will be in blocks. Block size will be selected to enhance blinding and maintain balance in the treatment allocation ratio as recruitment progresses

3.10 Home visit

As soon as possible after discharge from hospital, patients will be visited at home by a project field worker to collect information on social economic and environmental risk factors that may predisposes an individual child to develop severe anaemia. A housing survey will be conducted during this visit to determine possible risk factors for malaria which might act as confounders in determination of the primary trial end-point. Field workers will interview the parents/guardians of study subject to record characteristics about the house that might influence mosquito biting behaviour. These items will include building material, an evaluation of the presence of eaves, impregnation and condition of bed nets. During the visit, parents will be encouraged to protect the study child with a bed net.

3.11 First OPD visit after discharge from hospital

One week after discharge, study subjects enrolled in the study will be asked to return to the OPD clinic for routine assessment. At this visit a fingerpick blood samples will be collected for haemoglobin measurement and thick blood film examination for malaria parasite. The first dose of trial medication will be given during this visit. Any medical condition detected during the visit will be treated.

3.12 Randomisation

Children will be individually randomized into either the SP or the placebo group in a 1:1 ratio, using permuted blocks of 12 generated by computer using the STATA program. Blocks will not split across centres. Tablets (enough for 6 doses) will be packed into envelopes bearing the randomization number. The next envelope in sequence will be assigned to the child at the time of their admission to hospital. The randomisation code will be kept in sealed opaque envelopes by the local safety monitor and the MRC Laboratories accountant who alone will know the code, which associates each treatment group with either S/P or placebo.

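### Section 3.12 allocates at admission, but section 3.9 and the Summary allocate at or after the end of hospital treatment; followed literally, 3.12 puts children who die or leave before any dose into the ITT set

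*Protocol*

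**What the plan says.** Four places in the protocol bear on when a child is allocated and when treatment starts.

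- Section 3.12 (Randomisation): "The next envelope in sequence will be assigned to the child at the time of their admission to hospital". The same section says that these envelopes hold the child's tablets, carry the randomisation number and come from permuted blocks of 12 kept within centre.
- Section 3.9 (Discharge from hospital): children are "individually randomised into either the S/P or the placebo group in a 1:1 fashion at the time of discharge from hospital". It adds that chemoprophylaxis waits a further week, because antimalarials are likely to have been given in hospital.
- Summary: "After receiving treatment from the hospital, 1200 Gambian children with a haemoglobin concentration of less than 7 g/dL will be randomised". This agrees with 3.9.
- Section 3.11 (First OPD visit): "One week after discharge, study subjects enrolled in the study will be asked to return to the OPD clinic for routine assessment", and "The first dose of trial medication will be given during this visit".

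Section 3.20 makes the primary analysis intention to treat. Section 3.22 allows for 15% drop-out, described as occurring during follow-up. Section 3.6 separately dates the follow-up visit at 7 days after admission, whereas 3.11 dates it one week after discharge.

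**The concern.** With numbered envelopes used in order, giving a child the next envelope is the act of allocation. Sections 3.12 and 3.9 therefore set two different starting points for the trial. Under 3.12 the randomised set includes every child who dies on the ward, is taken home early or does not return for the first dose. Under 3.9 the inpatient losses fall outside it, and only the week between discharge and first dose remains exposed.

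Trial medication cannot have affected a child lost before the first dose. Such a child either has no end-of-season haemoglobin, which adds to missing data on the primary endpoint, or is measured while untreated, which pulls the two arms together. Some loss of this kind is foreseeable. The Summary says of children admitted with severe anaemia that "about 10% of such children die", and section 3.6 describes inpatients with respiratory distress, impaired consciousness and need for immediate transfusion. Several sites enrol, and each needs a single rule.

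**Working it through.** **Step 1. The texts side by side.**

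| Place | Moment of allocation | Gap before first dose |
|---|---|---|
| 3.12 | Admission | Hospital stay plus about one week |
| 3.9 | Discharge | About one week |
| Summary | After hospital treatment | Consistent with 3.9 |

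The first dose is fixed by 3.11 at the OPD visit one week after discharge. No section explains the difference or says which rule governs.

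**Step 2. Reproduce the plan's sample size.** Inputs from section 3.22: control proportion 0.20; 34% reduction, so 0.20 × 0.66 = 0.132; power 80%; drop-out 15%; N = 1200. The 5% level is stated there for the malaria endpoint; two-sided 5% is assumed for both endpoints.

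n per arm = [1.96·√(2p̄(1−p̄)) + 0.8416·√(p1(1−p1) + p2(1−p2))]² / (p1−p2)², with p̄ = 0.166. The two square roots are 0.5262 and 0.5240, and p1−p2 = 0.068.

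- No continuity correction: 469 per arm; 938/0.85 = 1104.
- With continuity correction: 498 per arm; 996/0.85 = 1172, within 3% of 1200.

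The stated figure is reproduced with the correction.

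**Step 3. Power as planned.** Evaluable per arm = 600 × 0.85 = 510.

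z = [0.068·√510 − 1.96 × 0.5262] / 0.5240 = 0.962, so power is 83.2% (no correction).

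**Step 4. Add a loss between allocation and first dose.** The protocol gives no figure, so the loss L is an assumption. If lost children have no primary outcome and L comes on top of the 15%, evaluable per arm = 600 × (1−L) × 0.85, and N needed = 938 / [0.85(1−L)].

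| L assumed | Evaluable per arm | Power for 34% | N needed for 80% |
|---|---|---|---|
| 0 | 510 | 83.2% | 1104 |
| 2% | 499.8 | 82.5% | 1127 |
| 5% | 484.5 | 81.3% | 1162 |
| 10% | 459 | 79.2% | 1227 |
| 15% | 433.5 | 76.8% | 1299 |

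With the continuity correction (996 in place of 938), N needed is 1234 at 5% and 1302 at 10%, so the method that best reproduces the plan leaves less slack.

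**Step 5. Alternative handling.** Suppose never-dosed children in the S/P arm are still measured and kept at the control rate, with 510 evaluable per arm. The S/P proportion becomes 0.20L + 0.132(1−L).

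| L assumed | Diluted reduction | Power |
|---|---|---|
| 2% | 33.3% | 81.6% |
| 5% | 32.3% | 78.9% |
| 10% | 30.6% | 74.1% |
| 15% | 28.9% | 68.9% |

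**The case against.** The best defence is that 3.12 is a slip in one sentence. Section 3.9 and the Summary agree with each other, 3.9 gives a reason for the week's delay, and exact analysis sets are usually left to the analysis plan, which is not shown. This is fair as to likely intent. But 3.12 is the section that tells staff how to allocate, and the moment of allocation is trial conduct that no later analysis plan can repair.

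The defence is stronger on size. A reader might apply the Summary's 10% to 1200 children and infer about 120 deaths before any dose. The documents do not support that. The figure is background mortality for severe anaemia in tropical Africa, it is not split into before and after discharge, and the trial enrols at haemoglobin below 7 g/dL, while its own endpoints call below 5 g/dL severe. Losses of 2% to 5% leave uncorrected power above 80% in step 4. If some of the loss is already inside the 15% allowance, the effect is smaller still.

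A reader might also infer that the mortality comparison would be heavily diluted. The protocol gives no death counts by arm from which to calculate this. Deaths are a secondary endpoint counted during the surveillance period, and section 3.14 can be read as starting that period after discharge, which would leave inpatient deaths out. No start is fixed, so the point supports defining time zero and no more.

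Finally, nothing shows that centres would in fact follow different sections. That remains a possibility that the text leaves open.

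**Conclusion.** The contradiction is real and unreconciled, and the ITT population depends on which section is followed. Under 3.12 as written, children who die in hospital or do not return for the first dose are randomised.

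The consequence is dilution and missing primary outcomes. A reader might infer a bias towards one arm, but as long as allocation is concealed before the first dose, loss in that interval should not depend on arm.

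The cost in power is modest: about 1 to 6 percentage points over an assumed loss of 2% to 15% (83.2% down to between 82.5% and 76.8%), and somewhat more if undosed children are measured and retained. These figures rest on an assumed loss that is additional to the 15% drop-out, a two-sided 5% test and no continuity correction. The reason to act is that the protocol must have one moment of allocation; the power figures alone would not compel it.

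**What to change.** State one allocation time in both sections.

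- Minimum: amend 3.12 so that the next envelope is assigned at discharge, in agreement with 3.9 and the Summary. About a week before the first dose stays exposed to loss.
- Preferred: in both 3.9 and 3.12, assign the next envelope at the first OPD visit, immediately before the first dose. This closes the gap.

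In either case, count ITT membership and all follow-up time from that moment. Do not repeat the haemoglobin entry criterion there: section 3.6 keeps children in hospital until haemoglobin has risen, so a literal re-check of below 7 g/dL would exclude recovering children and change the trial population.

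Reconcile the follow-up visit in 3.6 (7 days after admission) with that in 3.11 (one week after discharge), since allocation may be tied to it.

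The cost is small. The wording changes, tablet envelopes must be on hand and used in sequence within each centre at the later point, and children lost before it are logged but not randomised. The target of 1200 is then counted from the new moment.
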